### *List of Abbreviations*

|        |                                                                                                                            |
|--------|----------------------------------------------------------------------------------------------------------------------------|
| GCP    | Good Clinical Practice                                                                                                     |
| ICH    | International Conference on Harmonisation                                                                                  |
| IMP    | Investigational Medicinal Product                                                                                          |
| ISF    | Investigator Site File                                                                                                     |
| TMF    | Trial Master File                                                                                                          |
| SOP    | Standard Operating Procedure                                                                                               |
| CRF    | Case Report Form                                                                                                           |
| AE     | Adverse Event                                                                                                              |
| SAE    | Serious Adverse Event                                                                                                      |
| AR     | Adverse Reaction                                                                                                           |
| SAR    | Serious Adverse Reaction                                                                                                   |
| UAR    | Unexpected Adverse Reaction                                                                                                |
| SUSAR  | Suspected Unexpected Serious Adverse Reaction                                                                              |
| ACCORD | Academic and Clinical Central Office for Research & Development - Joint office for University of Edinburgh and NHS Lothian |

## *Summary*

Chronic pelvic pain (CPP) affects >1 million UK women. Annual healthcare costs are estimated at >£150 million. Proven interventions for CPP are limited and treatment is often unsatisfactory. Gabapentin is increasingly prescribed due to reports of effectiveness in other chronic pain conditions, but there are insufficient data supporting value in CPP specifically. The mechanism of action of gabapentin in CPP is also unclear. Given the prevalence and costs of CPP, we believe a large multi-centre placebo-controlled double-blind randomised-controlled trial (RCT) to evaluate the efficacy of gabapentin in management of CPP is required along with exploration of its mechanism of action. The focus of this study is a pilot to inform planning of a future RCT. We aim to recruit 60 women with CPP in NHS Lothian and NHS Grampian and randomise them to gabapentin or placebo. Response to treatment will be monitored by questionnaire at 3 and 6 months. A random subset of 24 Edinburgh women will undergo functional magnetic resonance imaging of the brain at 3 months. Our primary objective is to assess recruitment and retention rates and to obtain data to refine the research methodology for the RCT. We also aim to perform a pre-trial cost-effectiveness assessment of treatment with gabapentin.

# 1 INTRODUCTION

## 1.1 BACKGROUND

Chronic pelvic pain (CPP) affects over 1 million women in the UK (Latthe 2006); Daniels & Khan 2010). It is the reason for 20% of gynaecological consultations and causes a 45% reduction in work productivity (Cheong 2006). The annual cost for caring for UK women with CPP has been estimated at £154 million (Cheong 2006). The pathogenesis of the painful symptoms experienced by women with CPP is poorly understood. They are associated with specific pathological processes, such as endometriosis, but up to 55% of women with CPP appear to have no obvious underlying pathology (Daniels & Khan 2010). The management of CPP is difficult (Stones & Mountfield 2000) because in the absence of underlying pathology, no established gynaecological treatments are available.

## 1.2 RATIONALE FOR STUDY

Gabapentin (a GABA analogue) is being increasingly prescribed in general practice for CPP. It is also recommended by some practitioners as a treatment of choice for CPP in a multi-disciplinary setting, despite no evidence on which to base this recommendation, and no clear mechanism of action. To our knowledge, only one study has evaluated the use of gabapentin for CPP. This small study (56 patients) compared gabapentin against amitriptyline for treatment of CPP and showed that gabapentin had greater efficacy (80% compared to 70% improvement in pain scores at 12 months) (Sator-Katzenschlager 2005). Unfortunately, this study had no placebo arm and the significance of the effect on quality of life provided by gabapentin in the management of CPP was not evaluated. Nevertheless, the efficacy of gabapentin has been documented for other chronic pain conditions: painful diabetic neuropathy, postherpetic neuralgia, mixed neuropathic pain conditions, spinal-cord injury and phantom limb pain (Wiffen 2005). The number needed to treat for improvement in all trials with evaluable data is 4.3 (95% CI 3.5 to 5.7). In some of these trials, gabapentin also improved sleep, mood and other elements of quality of life.

Current understanding of the mechanism of action of gabapentin has relied on studies in non-specific disease models and animals using functional magnetic resonance imaging (fMRI) of the brain. This modality has been successfully employed to investigate nociceptive processing in humans and has shown that gabapentin is effective in modulating nociceptive transmission when central sensitisation is present (Iannetti 2005). In anaesthetised rats, fMRI has shown that gabapentin produces significant and discrete changes in brain activation (Governo 2008). However, a recent review has highlighted the need for studies of nociceptive processing, using fMRI, to further understanding of CPP (Vincent 2009). We believe that fMRI could also be used to investigate the mechanism of action of gabapentin in CPP, leading to further understanding of the pathophysiology of painful symptoms of CPP and the identification of novel treatment strategies.

Ideally, a definitive evaluation of the efficacy and mechanism of action of gabapentin in the management of CPP with no obvious underlying pathology requires a large multicentre randomised controlled trial (RCT). This is a pilot study to assess the processes that are vital to the success of such a trial.

# 2 STUDY OBJECTIVES

## 2.1 OBJECTIVES

### 2.1.1 Primary Objective

The primary objective is to determine whether it is possible to achieve acceptable recruitment and retention rates in two centres (NHS Lothian and NHS Grampian) within defined inclusion/exclusion criteria

### 2.1.2 Secondary Objectives

1. To determine the effectiveness and acceptability to patients of the proposed methods of recruitment, randomisation, drug treatments, use of brain fMRI and follow-up
2. To determine whether fMRI of the brain a sensitive approach to determine the mechanism of action of gabapentin in the management of CPP
3. To determine whether gabapentin is likely to be cost effective given the current level of evidence and uncertainty, and to ascertain what further evidence is needed for the evaluation of gabapentin

## 2.2 ENDPOINTS

### 2.2.1 Primary Endpoints

1. The proportion of eligible patients randomised into the study.
2. The proportion of randomised patients who take all their medication and fully complete questionnaires at final follow up.

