### 6 months(+/- 7 days) **Visit 4**

Questionnaire  
Unblinding  
Collection of treatment diary  
Collection of any unused study medications

3 - 6 months              Focus groups (subset)

The following measures will be completed by the subject in a daily treatment diary beginning on Day 1 of treatment.

- Time and dose of gabapentin taken
- Reason for any change in trial medication dose
- Concomitant medications taken
- Alternative therapies used
- Any visits to a healthcare professional
- Adverse events
- Weekly average Lickert pain score

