## 9 STATISTICS AND DATA ANALYSIS

### 9.1 SAMPLE SIZE CALCULATION

We have used a confidence interval (CI) approach (Thabane 2010) to estimate the sample size to establish feasibility based on a loss to follow-up of <20%. A 95% CI for 20% of 60 patients (12/60) is 11% to 32%. We estimate that we will recruit ~3-4 patients per month from each centre and aim to recruit 60 patients over a nine-month recruitment period. Each centre performs 6-7 laparoscopies per month that fit the inclusion criteria. A power calculation for the fMRI sub-studies is more difficult due to the complexity of the model (Mumford and Nichols 2008). The signal noise ratio changes in space and therefore power depends on the effect size that differs from region to region. We have estimated that we will need to recruit 24 women to determine where there are differences using fixed effect analyses

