### 9.2 PROPOSED ANALYSES

#### (i) Determine recruitment and retention rates in two centres

Using the information collected from the participant log, we will determine the number of patients recruited from the pool of eligible women and a >50% recruitment will be deemed acceptable. While a retention rate of 100% would be ideal, we will consider a rate of 90% satisfactory. We will provide an estimate of the proportion and its 95% confidence interval. In addition, we will determine the nature and number of unanswered questions in each questionnaire and identify reasons for non-response through the focus groups and participant interviews in order to optimise data collection in the future trial.

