#### (ii) Effectiveness and acceptability of proposed methods of recruitment, randomisation, drug treatments, questionnaires, use of brain fMRI and follow-up?

These areas will be explored in the focus group discussions and assessed quantitatively using additional questions included in participant questionnaires administered at 6 months. Due to the conflicting literature about the benefits of methods such as prescription monitoring, pill counting and devices for monitoring the self-administration of medicines (Melnikow and Kiefe, 1994), data on blinding and compliance to treatment will be derived from questionnaires at 6 months. We aim to determine if treatment is acceptable in terms of self-reported compliance (from treatment diaries). Although this is a pilot study and the sample size is small, we will assess the effect of any non-compliance on the LICKERT score by performing protocol and intention to treat analyses. This information along with health professionals' and clinical research nurses' views (as assessed by questionnaire) will be used to inform the design of the future RCT. (iii) Sensitivity of brain fMRI to study the effect of gabapentin in the management of CPP

The fMRI data will be analysed using a voxelwise approach and hierarchical linear modelling. An ANOVA [pre/post treatment\*gabapentin/ placebo] will be performed to investigate which areas of the brain gabapentin acts on compared to placebo. A regression analysis between brain activity and the behavioural measures will also be performed to evaluate the relationship between gabapentin brain activity and pain reduction. The brain fMRI scan results will then be compared with other studies of gabapentin (Iannetti 2005, Governo 2008) to determine the sensitivity of this approach to study the mechanism of action of gabapentin in CPP. We will use published fMRI methodology (Mumford & Nichols 2008) informed by the pilot to power future fMRI studies.

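### Primary endpoint 2 is a stricter composite than the retention named in the objective, the sample size and the 90% criterion, and the protocol never says which quantity is judged

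*Protocol*

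**What the plan says.** Four places in the protocol bear on this point.

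- **Objective (2.1.1).** The aim is to "determine whether it is possible to achieve acceptable recruitment and retention rates in two centres". Drug adherence and questionnaire completeness are not mentioned.
- **Endpoint (2.2.1, item 2).** "The proportion of randomised patients who take all their medication and fully complete questionnaires at final follow up". The denominator is all randomised women, and both conditions must be met.
- **Sample size (9.1).** The authors "estimate the sample size to establish feasibility based on a loss to follow-up of <20" per cent, and give a 95% interval of 11% to 32% for 12 lost out of 60.
- **Criterion (9.2(i)).** "While a retention rate of 100% would be ideal, we will consider a rate of 90% satisfactory". An estimate with a 95% confidence interval is promised. Unanswered questions are a further analysis alongside it.

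Compliance is taken up in 9.2(ii), under acceptability. One sentence there says that "data on blinding and compliance to treatment will be derived from questionnaires at 6 months"; the next refers to self-reported compliance from the treatment diaries. Section 5.5.4 separates withdrawal from treatment from withdrawal from the trial. Section 5.5.3 keeps women whose code has been broken in follow-up after they stop the study drug.

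**The concern.** A pilot's primary endpoint should be the quantity that its objective names, its sample size addresses and its success criterion judges. Here the last three refer to staying in the study, while the endpoint adds complete drug intake and complete questionnaires.

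Followed literally, the plan leaves two options. Either a retention threshold is applied to a stricter composite, or the 90% criterion and the sample-size statement have no primary endpoint that matches them. The choice would be open after the data are seen, and the two options can give opposite answers on whether follow-up in the future RCT is feasible.

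**Working it through.** **1. The plan's own figure.** The exact (Clopper-Pearson) 95% interval for 12/60 is 10.8% to 32.3%, which rounds to the stated 11% to 32%. The arithmetic is right, but it describes loss to follow-up and gives no precision for the composite.

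**2. Does the protocol treat the components as part of retention?**
- Unanswered questions: an additional analysis in 9.2(i), beside the retention estimate.
- Compliance: assessed under acceptability in 9.2(ii), with no threshold.
- Stopping the drug: distinct from leaving the trial (5.5.3, 5.5.4). A woman who stops the drug and stays in follow-up is retained but, on a plain reading, cannot have taken all her medication.

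**3. Ordering.** Write R for the proportion retained, and A and C for the proportions of retained women who take all medication and who leave nothing blank.

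Composite = R × P(both conditions met, given retained) ≤ R.

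- R = 90% (54/60): every retained woman must meet both conditions. One failure gives 53/60 = 88.3%.
- R = 95%: 0.90/0.95 = 94.7% of retained women must meet both.
- R = 100%: 90% must meet both.

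**4. Illustrations.** The protocol gives no values for A and C, so those below are assumed. With independence, composite = R × A × C. The last column is the binomial probability of at least 54 successes in 60, the count that corresponds to 90%.

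| R | A | C | Composite | P(at least 54/60) |
|---|---|---|---|---|
| 90% | 90% | 90% | 72.9% | 0.001 |
| 95% | 90% | 90% | 77.0% | 0.008 |
| 95% | 95% | 95% | 85.7% | 0.23 |
| 100% | 90% | 90% | 81.0% | 0.046 |
| 100% | 95% | 95% | 90.2% | 0.63 |

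For retention alone, the same probability is 0.61 at R = 90% and 0.97 at R = 95%.

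**5. Sensitivity to independence.** Take R = 95%, A = C = 90%.
- Least overlap: 0.95 × (0.90 + 0.90 − 1) = 76.0%, probability 0.005.
- Full overlap: 0.95 × 0.90 = 85.5%, probability 0.21.

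Both are far below the 0.97 for retention alone.

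**6. Precision if the criterion is tied to retention.** Observing 54/60 gives an exact 95% interval of 79.5% to 96.2%.

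**The case against.** The strongest defence is structural. The objective has two parts, there are two primary endpoints, and 9.2(i) gives two criteria in the same order: recruitment above 50%, retention 90%. Read one to one, endpoint 2 is how the authors measure retention. That reading is possible, but the protocol never states it. It also fits poorly with a sample size based on loss to follow-up, with unanswered questions analysed additionally, and with women who stop the drug but remain in follow-up. The need to make the link explicit stands.

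It is also fair to say that this is a 60-woman pilot with no hypothesis test or automatic stop/go rule on this figure, and that adherence cut-offs and scorability rules may sit in an analysis plan not shown here. Which quantity is primary and judged at 90% is a different matter: the protocol itself fixes the endpoint and the threshold.

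A reader might infer four stronger claims that the documents do not support.

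- **That the endpoint is bound to fail.** No adherence or completion rates are given, and the table includes a case that reaches 90%.
- **That a low composite could not be explained.** The participant log (section 8) records early leavers and reasons, the diary (6.5) records daily drug use, and 9.2(i) analyses unanswered questions.
- **That the compliance sources contradict each other.** Diary and 6-month questionnaire are both planned self-report sources. What is missing is a rule on which one decides.
- **That returned capsules ought to be counted.** Visit 4 includes "Collection of any unused study medications", but 9.2(ii) gives a reason for not relying on pill counts: conflicting literature on such methods.

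Nor is the medication without any reference. The research team advises the dose weekly until the optimum is reached (6.3), so intake can be judged against the dose advised.

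**Conclusion.** The point holds as a mismatch between stated quantities. That part rests on the text and needs no assumption: endpoint 2 is stricter than retention, can never exceed it, and is not identified as the retention that 9.2(i) judges. At exactly 90% retention, a single lapse by one retained woman separates the two.

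The size of the gap is conditional. With 95% retained and 90% meeting each further condition independently, the composite is about 18 points below retention (95% − 77%), and the chance of reaching 54/60 falls from 0.97 to 0.008. With the overlap between the two conditions unknown, the gap is 9.5 to 19 points. It shrinks as adherence and completeness approach 100%. The practical consequence is that one set of results could be reported as satisfactory or unsatisfactory, according to which quantity is compared with 90%.

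**What to change.** - **2.2.1 and 9.2(i):** define retention as the proportion of all randomised women who provide the 6-month questionnaire. Apply the 90% criterion and its 95% confidence interval to this proportion only.
- **9.1:** state that the loss-to-follow-up calculation refers to the complement of this same proportion.
- **2.2.1:** report adherence, relative to the dose advised, and questionnaire completeness as two separate proportions of all randomised women. Keep the composite as a descriptive figure without a threshold.
- **9.2(ii):** state whether the diary or the 6-month questionnaire decides compliance when they disagree.

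The cost is rewording and three figures to report instead of one. No extra visits, participants or data are needed, because the log, diary and questionnaires already supply each component.

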### 2.2.2 Secondary Endpoints

The remaining data (effectiveness and acceptability of proposed methods of recruitment, randomisation, drug treatments and questionnaires use of brain fMRI and follow-up; and sensitivity of brain fMRI to study the effect of gabapentin in the management of CPP) will be used to refine the research methodology for the RCT.

# 3 STUDY DESIGN

A two-arm parallel randomised controlled pilot trial. This will be a two centre pilot study with sites in NHS Lothian and NHS Grampian. We will recruit 60 patients over approximately nine months. After randomisation the participants will receive treatment for six months. Participants and the health care team will be unblinded at the end of their treatment.

## 4 STUDY

### 4.1 NUMBER OF PARTICIPANTS

60 women aged 18-50 with a history of pelvic pain (cyclical or non-cyclical) and/or dyspareunia will be invited to participate in the trial.

### 4.2 INCLUSION CRITERIA

- Women aged between 18-50
- Pelvic pain of > 6 months
- Pain located within the true pelvis or between and below anterior iliac crests, associated functional disability
- No obvious pelvic pathology at laparoscopy (<3 years and >2 weeks ago)
- Using effective contraception

### 4.3 EXCLUSION CRITERIA

- Known pelvic pathology eg endometriosis, cyst
- Taking gabapentin or pregabalin or any restricted medications
- Due to undergo surgery in the next 6 months
- History of renal impairment
- Allergic to gabapentin
- Breast feeding
- Pregnancy or planning pregnancy in the next 6 months

## 5 PARTICIPANT SELECTION AND ENROLMENT (See flowchart for recruitment strategy – Appendix 5)

### 5.1 IDENTIFYING PARTICIPANTS

Women will be identified by their clinician and asked if they will talk to a member of the clinical research team. If they agree, they will then be given a patient information sheet and will be asked if they are happy to be contacted to get their decision on whether they wish to participate. This will give them ample time to read the patient information sheet, ask any questions and make an informed choice of whether to participate or not.

### 5.2 CONSENTING PARTICIPANTS

Eligible participants will be consented by a member of the clinical research team.

### 5.3 SCREENING FOR ELIGIBILITY

If participants express an interest in the study they will be assessed to determine whether they fulfil all the potential eligibility criteria.

### 5.4 INELIGIBLE AND NON-RECRUITED PARTICIPANTS

The following information will be monitored and collected:

- Demographic information (age, current medication)
- Reason for not entering the randomisation phase

### 5.5 RANDOMISATION

#### 5.5.1 Randomisation Procedures

Eligible women will be randomised to either gabapentin or placebo using a web-based system. Women will be stratified by centre (Edinburgh and Aberdeen). We will use randomised blocks of varying sizes.

#### 5.5.2 Treatment Allocation

After randomisation, participants will be allocated an oral treatment pack containing either gabapentin or placebo, both of identical appearance. There will be a drug protocol to follow in their treatment diaries. The same protocol will be used for the placebo. The participants will be allowed to use other medication (including analgesics) throughout the study period. The participant will be advised to use effective contraception throughout the study and for one week after.

#### 5.5.3 Emergency Unblinding Procedures

The blinding code will only be broken in emergency situations for reasons of patient safety, where knowledge of the treatment administered is necessary for the treatment of a serious adverse event or when required by local regulatory authorities. Participants whose randomisation codes are broken will cease treatment with the study drug but will continue to be followed up. The Investigator must document the reason for breaking the blind in the participant's source documents and in the Investigator Site Master File.

